#### Standard counselling

This will be performed in the control group, based on the institutional and national policy for breastfeeding (Resolution 412 of the year 2000). During pregnancy, women receive a group talk about the importance of breastfeeding as part of the maternity preparation course at the institution. During labour, early contact and early initiation of breastfeeding is supported by health workers at the institution who identify the risks for the woman-child dyad. During hospital discharge, women receive nutritional recommendations with an emphasis on EBF during the first 6 months. During the first 4 months postpartum, the follow-up time of the study, it is estimated that women in the control group will attend two follow-up growth and development visits, where the weight and length of the child is evaluated and breastfeeding support is given by group activities or individual consultation carried out by health professionals. The intervention group will also receive this standard follow up, as well as the new approach in EBF counselling. Table 2 summarizes the main characteristics of the new approach compared with the standard counselling given by the institution.

**Table 2 Tab2:** Time-points and description of breastfeeding counselling among control and intervention groups

Time-point	Intervention group		Control group	
	Issues to follow	Responsible	Standard care	Responsible
Last month of gestation	1. Dialogue with the women to determine risk of possible breastfeeding problems: - Fears and expectations - Breast examination - Breastfeeding problems - Intention to breastfeed 2. Maternal empowerment - Knowledge of familiar and social environment - Motivation - Early contact (skin to skin contact) - Commitment 3. Agreed solutions - Individuality respect - Realistic and assertive solutions	Researcher	Information on the benefits of breastfeeding and breastfeeding positions through a one-hour group talk as part of the institution’s course on preparation for motherhood.	Nursing Department
24 h postpartum	1. Dialogue with the women to evaluate problems and difficulties identified at gestation: - Fears and expectations - Early breastfeeding - Skin to skin contact - Adequate latching and suckling - Human milk volume 2. Maternal empowerment - Breastfeeding crisis: fatigue, fears and worries. - Motivation 3. Agreed solutions - Respect for individuality - Realistic and assertive solutions.	Researcher	Institutional policy to allow rooming in, skin to skin contact. Risks of early weaning. Nutritional recommendations about breastfeeding importance at hospital discharge.	Institutional health care professionals
1 month postpartum	1. Dialogue with the women to follow up the agreed solutions and identify new difficulties with breastfeeding - Maternal perception of milk volume produced - Maternal perception of infant appetite 2. Maternal empowerment - Fears and expectations: low breast milk volume - Motivation and solutions follow up - Self-esteem 3. Agreed solutions - Individuality respect - Solutions follow up and measure of breastfeeding achievements	Researcher	Six visits during the first 12 months to follow up infant growth and development. It includes education in breastfeeding in group meetings. Breastfeeding counselling on demand or by referral.	Institutional health care professionals: Nurse Department
3 months postpartum	1. Dialogue with the women to follow up agreed solutions and identify new breastfeeding difficulties: - Back to work, study and other activities. - Early initiation of complementary food 2. Maternal empowerment - Fears and expectations - Motivation and follow up of solutions - Self-esteem 3. Agreed solutions - Individuality respect - Solutions follow up and measure of breastfeeding achievements	Researcher	Six visits during the first 12mo to follow up infant growth and development. Lack of adherence to the program.	Institutional health care professionals, Prevention and promotion programs at the institution.

#### Measures

Questionnaires and assessments will be used to collect information among intervention and control groups at specific time-points, as shown in Table 1.
Maternal socioeconomic and demographic information, pregnancy information and paternal information: Information about residency, age, marital status, occupation, socioeconomic level, family size, family income, educational level, maternity leave, access to public services, social security, health benefits, smoking, alcohol consumption, family and medical history will be recorded. Gestational age will be determined by the date of the last menstruation, corroborated by sonographic studies available in the clinical notes. Paternal information will be reported by the woman and will include health status and monthly income.Intention to breastfeed: The scale uses five simple questions to determine the method of feeding that the woman plans for the baby. The scale has been validated and translated in previous studies [60].Maternal anthropometry: Anthropometric data - weight, height and mid upper arm circumference (MUAC) - will be collected in the last month of pregnancy, 24 h postpartum, and 1, 3 and 4 h months postpartum in minimal clothes. Weight will be measured in duplicate using an electronic scale (SECA 813, capacity 200 kg, precision 100 g), height measured in triplicate using a portable stadiometer (SECA 213, up to 205 cm) and MUAC measured in triplicate to the nearest cm (SECA 203 measuring tape, range 0 to 205 cm, graduation 1 mm). Weight gain during gestation (self-reported weight at the end of gestation minus pre-gestational weight) will be used as a baseline characteristic and as a covariate to predict the main outcomes.Breast examination: Participants will complete a questionnaire using illustrations of breasts to identify possible anatomical aspects that could make breastfeeding difficult (e.g. large breasts, flat nipples). This information will be used to focus the intervention for individual mothers.Edinburgh Postnatal Depression Scale (EPDS): This consists of 10 questions about feelings during the last week. It will be administered during the last month of gestation and 1 month postpartum as a tool to determine the risk of postpartum depression [54].Counselling register and evaluation: To assess the content of and adherence to the new EBF counselling intervention, a record of the problems identified will be kept during each visit. A questionnaire will also be administered by an independent investigator blinded to group allocation at the end of the study period (four months postpartum) which will include information on the problems identified, solutions and success, measured as: not successful (no problem resolution); limited success (partial resolution of the problem), or successful (problem solved).IPAQ short version: Physical activity questionnaire which considers types of physical activity, time (minutes per day) and number of days per week, and number of hours per day that the woman remains seated [61].Maternal food consumption: Determined using a standard food frequency questionnaire used and adapted in Colombian populations in other studies, and two multiple steps 24-h recall questionnaires to determine food consumption and nutrient intake including supplements, vitamins, minerals and maternal feeding problems; to be used as a baseline descriptive characteristic and as a potential confounder. This methodology is based on that described by the United States Department of Agriculture [58, 59]. To improve the quality of the data, photographs will be used to determine portion size [70]. Data analysis will be conducted using Colombian food composition tables [71], USDA standard nutrient reference database and food labels.Delivery information: Data about the type of delivery, newborn APGAR score, time of breastfeedng initiation, maternal-infant complications including those which delay the initiation of breastfeeding, and drugs administered during labour and the first 4 months after delivery.Newborn and infant anthropometry: Anthropometric variables - weight, length, MUAC and head circumference - will be measured by a trained nutritionist and dietitian following WHO protocol [72] at birth and 1, 3 and 4 months postpartum. Infant weight will be measured in duplicate using an electronic baby scale (TANITA 1583 with precision of 10 g, capacity 200 kg), length measured in triplicate using an infantometer (SECA 417, folding mechanism and foot stop, measuring range up to 100 cm), and head circumference and MUAC measured using a pediatric tape measure (SECA 201, range 0 to 205 cm, graduation 1 mm). Infant growth velocity will be defined as the change in the Z-score of weight for length, length for age, head circumference for age and mid upper arm circumference for age from birth to four months according to WHO growth standards [73]. Data collection will be performed by the same researcher in both groups to control information bias among observers.Breastfeeding information: This questionnaire collects information about initiation of breastfeeding at the hospital.Infant 24-h dietary recall: To determine the EBF prevalence, an infant 24-h recall will be used asking mothers about the foods consumed by the child during the previous day and infant feeding practices at 1, 3 and 4 months. = The counsellor will ask about the initiation, frequency and mode of preparation of specific beverages and semisolid foods or supplements since the last visit. This methodology will allow breastfeeding to be classified as exclusive or predominant according to WHO definitions [12].Breast-latching observation: Considers information about position of breastfeeding and maternal-infant perception of comfort during breastfeeding. This is a check-list that the investigator completes after watching a breastfeed [74].Breast milk macronutrients: Expression of breast milk (fore milk) will be performed at 1 and 4 months postpartum at the researcher’s office in the morning, using a Philips Single Electric Breast Pump under researcher supervision. The sample will be stored at − 20 °C in the laboratory at the Pontificia Universidad Javeriana for analysis. Content of macronutrients (carbohydrate, protein and fat) and energy in breast milk will be determined using the MIRIS Human Milk Analyzer, which uses infrared transmission spectroscopy and requires a human milk sample of 5 ml. Results will be recorded in the database.Breast milk prolactin: Determination of breast milk prolactin concentration will be performed using an Abcam ab226901 Human Prolactin SimpleStep ELISA kit. The procedure requires 2 ml of breast milk.Serum prolactin: To determine the maternal serum prolactin concentration, a non-probabilistic convenience subsample of 60 (20%) women will be selected. The blood sample will be taken at the laboratory of the institution, within 2 h of waking in the morning and before any food is consumed. The procedure will require 5 ml of maternal blood, which will be analyzed by ELISA (Abcam ab226901).

All questionnaires and assessments will be administered by the researcher.

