### Hypotheses and outcome variables

#### Primary hypotheses

Compared to standard management, the implementation of a new EBF counselling intervention for overweight woman will result in:
i)an increase in the prevalence of breastfeeding and EBF from birth up to four months of age;ii)slower infant weight for length growth from birth up to four months of age;iii)an increase in weight loss after delivery up to four months postpartum.

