#### Secondary hypotheses

Compared to standard management, the implementation of a new EBF counselling intervention designed to support overweight woman will result in:
i)An increase in the volume of breast milk in ml as a result of an increase in serum prolactin levels in ng/ml, at 1 and 4 months.ii)Higher milk prolactin concentration and adequate macronutrient content of protein, lactose, fat and energy, at 1 and 4 months, which will in turn be associated with more optimal infant growth (based on WHO growth standards).

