### Secondary outcomes and variables

i)Maternal serum levels of prolactin and breast milk prolactin concentration and macronutrient content, measured at 1 and 4 months after delivery;ii)Estimated breast milk intake at 1 and 4 months according to WHO recommendations [53].

The study design is shown in Fig. 1 and a timeline of measurements in Fig. 2.

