	Breast milk macronutrient content	Protein, lactose and fat content in human milk
	Prolactin in maternal serum	Concentration of prolactin hormone in maternal serum, 2 h after maternal wake up
3 months postpartum	Maternal anthropometry	Weight and MUAC.
	Infant anthropometry	Weight, length, head circumference, MUAC.
	Breast examination	Nipple and breast observation.
	Counselling registry	Detected problems and concerted solutions, applicability of last meeting’s concerted solution
	Infant 24-h recall	Time, place, type of food.
	Breast milk intake	Number of breastfeeds per day and night, time per each breastfeed, appetite (mother’s perception).
	Macronutrients content in breast milk	Protein, lactose and fat content in human milk.
	Prolactin in maternal serum	Concentration of prolactin hormone in maternal serum, 2 h after maternal wake up.
4 months postpartum	Maternal anthropometry	Weight and MUAC.
	Infant anthropometry	Weight, length, head circumference, MUAC.
	Breast examination	Nipple and breast observation.
	Assessment of breastfeeding counselling	Successful of new approach in EBF counselling with 5 questions to assess concerted solutions.
	IPAQ SV	Physical activity registry: type of activity, time (minutes per day), number of days per week.
	Maternal 24-h recall	Five steps 24HR: fast list, frequently forgotten foods, meals and time, food consumption in the last 24 h within detailed registry and standardized recipes.
	Semi-quantitative food frequency intake	Diary, weekly or monthly intake of 107 foods, included in 8 food groups.
	Infant 24-h recall	Time, place, infant feeding in the last 24 h (including breastfeeding, infant formula or other type of foods given to the baby).
	Breast milk intake	Number of breastfeeds per day and night, time per each breastfeed, appetite (mother’s perception).

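### Milk fat and energy are read from fore milk only, which cannot show whether their content is adequate or how it relates to infant growth

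*Protocol article*

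**What the plan says.** Under Measures, the milk sample is defined by fraction and time: "Expression of breast milk (fore milk) will be performed at 1 and 4 months postpartum". The setting is also given: "at the researcher’s office in the morning, using a Philips Single Electric Breast Pump under researcher supervision". All macronutrients come from this sample: "Content of macronutrients (carbohydrate, protein and fat) and energy in breast milk will be determined using the MIRIS Human Milk Analyzer". The analyser "requires a human milk sample of 5 ml", and the prolactin assay takes a further 2 ml of milk.

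Under Secondary outcomes and variables, the outcome is "breast milk prolactin concentration and macronutrient content, measured at 1 and 4 months after delivery". Under Secondary hypotheses, item ii predicts "Higher milk prolactin concentration and adequate macronutrient content of protein, lactose, fat and energy, at 1 and 4 months", and goes on to tie this to more optimal infant growth against the WHO standards.

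The Sample size section limits milk and prolactin analyses to a convenience subsample of 60 women, 30 per group. Strengths and limitations mentions the milk-volume algorithm and the prolactin subsample, but not the use of fore milk.

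**The concern.** Fat concentration rises from the start to the end of a feed, and energy rises with it. This is general lactation physiology and is not stated in the document. A sample of fore milk alone therefore gives fat and energy values below those of the feed the infant takes.

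Adequacy is an absolute judgement, so a value that is low by construction cannot support it. With unbiased laboratory work and complete data, the trial could still report that overweight mothers produce milk short of fat and energy when the whole feed is not short. The growth hypothesis has a related problem: the exposure would be the composition of the first part of a feed, not of what the infant received. Fore milk alone does not let a later analysis recover whole-feed fat.

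**Working it through.** **Figures in the plan.** The document gives no fat value, energy value or standard deviation for milk, so there is no planned figure on this point to reproduce. The check is a comparison of the sampling rule with the hypothesis, followed by two illustrations.

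**1. Where the bias cancels and where it does not.** Let W be whole-feed fat, F fore-milk fat, and d = W − F the deficit, with d > 0.

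- Adequacy against a reference R: F − R = (W − R) − d. The deficit stays in full.
- Arm comparison: difference in mean F = difference in mean W − difference in mean d. If the mean deficit is the same in both arms, it drops out.
- Growth association: the slope on F equals the slope on W only if d is the same in every woman. Nothing in the stated sampling secures that. If d varies, the slope is distorted.

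**2. Size of the common deficit (all inputs assumed, none from the documents).** Fore-milk fat 1 to 2 g/dL below the whole expression; fat 9 kcal/g; whole-milk energy 65 kcal/dL.

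- 1 g/dL × 9 kcal/g = 9 kcal/dL; 9 / 65 = 13.8%
- 2 g/dL × 9 kcal/g = 18 kcal/dL; 18 / 65 = 27.7%

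**3. How large a between-arm shift might be.** The only document inputs that help are in Sample size: 22.8% exclusive breastfeeding (EBF) in controls and a difference of 23%, read here as percentage points, plus 30 women per arm in the subsample. Assume that the 23-point difference carries over to the subsample, and that EBF status by itself moves fore-milk fat by k standard deviations (SD) through breast fullness at sampling.

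- Arm shift = 0.23 × k. For k = 0.5 this is 0.115 SD; for k = 1 it is 0.23 SD.
- Standard error of the arm difference in SD units = √(2/30) = 0.258.
- Two-sided 5% false-positive rate with s = shift / 0.258: 1 − Φ(1.96 − s) + Φ(−1.96 − s).
- k = 0.5: s = 0.445, rate about 7%. k = 1: s = 0.891, rate about 14%.

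For scale, the true difference detectable with 80% power at 30 per arm is (1.96 + 0.84) × 0.258, or about 0.72 SD. The values of k are illustrative; the documents support no particular one.

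**The case against.** The strongest reply is that the trial's main question is a comparison of arms, and a deficit common to both arms largely cancels there. That stands. It does not rescue item ii of the secondary hypotheses, which speaks of adequate content and of a relation to growth.

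A reader might go further and infer that the intervention changes how often women feed, so that breasts are less full at sampling in the intervention arm and its fore-milk fat is falsely raised. The documents do not support this as a fact. The primary hypothesis is "an increase in the prevalence of breastfeeding and EBF from birth up to four months of age"; feeding frequency is not named as an effect, and nothing is said about breast fullness at the morning visit. Table 1 also collects the number of feeds by day and night, so a difference in feeding pattern could at least be examined. What remains is a possible bias of unknown size, probably small on the trial's own planning values.

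A reader might also fault the article for giving no interval since the last feed and no choice of breast. These are bench details that a condensed article may leave to the full protocol or a laboratory procedure. The article does fix time of day, place, pump and supervision. Their absence is not counted as an error here; the firm point is the stated choice of fore milk.

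Finally, full expression has its own costs. It takes longer, it removes milk from the breast before a feed, and it could disturb the prolactin measurements, since the Background describes a prolactin response to suckling. That objection is sound and shapes the fix.

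**Conclusion.** The point holds in a narrow form. Fore milk cannot represent the fat and energy of the whole feed, so neither the adequacy of fat and energy nor their link to infant growth can be judged from the planned sample. This conclusion needs only the stated sampling rule, the stated hypothesis and the general fact that fat rises during a feed. Protein and lactose are little affected.

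The 14% to 28% understatement of energy rests wholly on assumed inputs and shows an order of magnitude only. Confidence in any differential bias between arms is low, and the documents do not allow it to be sized. No primary outcome is touched, and the measures concerned are two components of a secondary outcome in 60 women. Severity is minor.

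**What to change.** In the Measures paragraph on breast milk macronutrients, replace fore milk with a full expression of one breast using the pump already planned. Mix the milk, take the 5 ml macronutrient aliquot from the mixture, record the time since the last feed from that breast, and return the remaining milk for the infant. To protect the prolactin outcomes, draw the serum sample before pumping, and take the 2 ml milk-prolactin aliquot from the same fraction in every woman at both visits. The cost is a change of wording and some extra pumping time per sample; pump, supervision, laboratory and aliquot volumes stay as they are.

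If only fore milk can be taken, label fat and energy as fore-milk values, withdraw them from item ii of the secondary hypotheses (adequacy and growth), and keep protein and lactose there. This costs nothing in the field but gives up the conclusion on fat and energy.

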#### Pilot study

Due to the lack of information about characteristics of overweight pregnant women in Bogotá, a pilot study was performed among pregnant women (*n* = 209) to determine maternal socioeconomic characteristics, anthropometric status, prenatal health status, intention to breastfed, physical activity and eating patterns. Briefly, 33.7% of participants were overweight in the last trimester of pregnancy, 23.7% gained more than 13 kg by the last trimester and among overweight women, 37.2 and 31.3% had a strong and very strong intention to breastfeed. The pilot study showed the prevalence of overweight among pregnant women in the planned study population was similar to that reported previously [55]. There was also a very high intention to breastfeed among overweight women, justifying the plan to develop and test a counselling intervention.

The pilot study was also an opportunity to test the questionnaires and validated scales (such as the intention to breastfeed scale) and to evaluate the time needed to complete the questionnaires. Following the pilot study, questions about breastfeeding practice were also changed to improve the maternal understanding of the questions.

#### Data management

To guarantee the quality of the data, four checks will be performed: i) double checking of the information recorded in the questionnaires; ii) breastfeeding support verification (questionnaire administered by an independent investigator) in all mothers who completed the follow up; iii) random selection of questionnaires to check the consistency between data entered in the database and questionnaires; and iv) preliminary database check to identify extreme data and missing data using IBM SPSS Statistics software version 24. The questionnaires containing the original information will be stored safely at the Pontificia Universidad Javeriana for five years and the digital database will be stored as a computer file with access code. Clinical visits for breastfeeding counselling will be scheduled on different days for control and intervention groups to avoid contamination bias.

